#### Exclusion criteria

Evidence of intracranial hemorrhage (ICH) or other cerebral diseases (e.g., vascular malformation, tumor, abscess or multiple sclerosis) on the CT or magnetic resonance imaging (MRI) scan.Patients who underwent thrombolysis or endovascular treatment.Known history of allergy or suspected allergy to the study drug.Fasting blood glucose <2.8 or >16.8 mmol/l or with severe complications due to diabetes (e.g., peripheral neuropathy, or diabetic gangrene).Liver function impairment with the value of alanine aminotransferase (ALT) or aspartate aminotransaminase (AST) over 1.5-fold the upper limit of normal range.Renal dysfunction with the value of serum creatinine over 1.5-fold the upper limit of normal range.Severe cardiac dysfunction on echocardiogram or the New York Heart Association (NYHA) heart functional class III or IV.History of prior stroke with a modified Rankin Scale (mRS) score ≥2.Atrial fibrillation complications.Severe stroke as assessed by appropriate imaging techniques (e.g., massive cerebral infarction affecting more than one lobe of the brain or over one-third of the blood-supply area of the middle cerebral artery).Legally disabled patients.Hemorrhagic tendency or severe or dangerous bleeding within the prior 3 months.Suspected alcohol addiction or drug abuse.Severe complications that would make the condition more complicated as assessed by the investigator.Women who are pregnant, lactating or have a positive pregnancy test, or women who plan to become pregnant in the subsequent 6 months.Women who have a menstrual period at baseline.Patients who are participating in other trials or have participated in other trials within the prior 3 months.

### Recruitment

Recruitment into the trial started in December 2012 and is estimated to end in December 2015. Patients with AIS will be screened for eligibility according to the inclusion and exclusion criteria. Patients will be thoroughly informed of the details of the study and its potential benefits and risks. Only those who meet the inclusion criteria and willingly agree to provide written informed consent will be included. This study will be conducted in 43 hospitals across China, and the number of hospitals could be increased after the interim analysis.

### Sample size estimation

The proportion of patients who had a favorable outcome, defined as a modified Rankin Scale (mRS) score of 0–1, after standard medical care coupled with placebo or DHI for 90 days was unclear. According to previous studies [10, 11], the proportion of patients who had a mRS score of 0–1 was about 28.7–45.2 % when only treated with placebo, so we estimate the proportion is 45 % when placebo coupled with standard medical care are used. In this trial, it is hypothesized that an increase of at least 10 % is of clinical significance for the DHI group. An adaptive design was selected and EAST5.2 software was used to calculate the statistical sample size. After calculation, the number of subjects was initially estimated to be 703 (one-sided test, α = 0.05, β = 0.2). To allow for a dropout rate of 20 %, a total of 846 patients will be recruited. According to the adaptive design, the sample size may be adjusted after the interim analyses, which will be carried out when one-third (282) and two-thirds (564) of patients have completed the trial, respectively. With a 2:1 randomization ratio, the number of participants in the DHI group is 564 and that in the control group is 282.

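### The 846 recruits do not quite cover the plan's own 20% dropout: if those patients give no day-90 mRS, about 677 remain instead of 703, and power is about 78.7% instead of 80%

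*Protocol article*

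**What the plan says.** All the figures are in the protocol article under Sample size estimation. On the control rate for a favorable outcome (mRS 0–1 at day 90) it says "so we estimate the proportion is 45 % when placebo coupled with standard medical care are used". On the effect, "it is hypothesized that an increase of at least 10 % is of clinical significance for the DHI group". With a one-sided α of 0.05 and β of 0.2, "the number of subjects was initially estimated to be 703". The dropout step follows: with 20% dropout allowed for, "a total of 846 patients will be recruited". No inflation formula is given.

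The same total then sets the arms, "With a 2:1 randomization ratio, the number of participants in the DHI group is 564 and that in the control group is 282", and the interim analyses, which are to be "carried out when one-third (282) and two-thirds (564) of patients have completed the trial". The Interim analysis section adds that a Lan-DeMets spending function with an O'Brien-Fleming boundary will be used.

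**The concern.** A dropout rate is a share of the patients recruited. To keep 703 after losing 20%, 703 must be 80% of recruitment, so the division is by 0.8. Adding 20% of 703 to 703 gives a smaller total, and 846 lies close to that smaller total. The stated 80% power would then not be the power of the trial as sized, at the dropout rate the plan itself assumes.

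The interim counts are also affected. They are thirds of the 846 recruited, yet they are defined on patients who have completed the trial. If fewer than 846 complete, 282 and 564 completers come later than one-third and two-thirds of the information.

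**Working it through.** **Inputs.** Control 45%, DHI 55% (10 points absolute), 2:1 allocation, one-sided α 0.05, power 80%, 20% dropout and 846 recruits, all from Sample size estimation. Two interim looks at one-third and two-thirds plus a final look, with Lan-DeMets O'Brien-Fleming spending, from Sample size estimation and Interim analysis.

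**Step 1: reproduce 703.**
- Both arms have p(1 − p) = 0.2475. With N/3 in control and 2N/3 in DHI, the variance of the difference is 0.2475 × 4.5/N = 1.11375/N.
- Fixed design: N = 1.11375 × (1.645 + 0.842)²/0.10² = 688.6.
- Three-look design: the boundaries are z = 3.200, 2.141 and 1.695. 80% power needs a drift of 2.5116, so N = 1.11375 × 2.5116²/0.10² = 702.6, which rounds up to 703. The inflation over the fixed design is 1.0203.

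This matches the plan's figure exactly. So 703 already contains the cost of the interim looks and contains no dropout allowance. The match also supports reading the 10% as an absolute difference.

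**Step 2: the dropout allowance.**
- 703/(1 − 0.20) = 878.75, so 879 (586 DHI + 293 control). This is 33 more than 846.
- 703 × 1.2 = 843.6, so 844. The next total divisible by 3 is 846.
- 846/703 = 1.203.

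**Step 3: what 846 yields.**
- At 20% loss: 846 × 0.8 = 676.8, about 677. Shortfall 703 − 677 = 26 (3.7% of 703).
- Largest loss that still leaves 703: 1 − 703/846 = 16.9%.

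**Step 4: power under the same three-look model.**

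| Evaluable N | Drift = 0.10/√(1.11375/N) | Power |
|---|---|---|
| 703 | 2.512 | 80.0% |
| 677 | 2.466 | 78.7% |

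**Step 5: interim counts as fractions of evaluable patients.**
- Of 677: 282/677 = 41.7% and 564/677 = 83.3%.
- Of 703: 282/703 = 40.1% and 564/703 = 80.2%.
- True thirds of 677 would be about 226 and 451; of 703, about 234 and 469.

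**The case against.** **Dropouts may still be analysed.** The Statistical analysis section refers to full analysis and per protocol sets according to intention-to-treat, and the mRS runs to 6 for death, so deaths are not missing. Some patients counted as dropouts could therefore have a day-90 score. At 15% effective loss, 846 leaves 719 and power is 80.8%. This stands as a condition: 677 is the yield only if the full 20% give no primary-outcome data, and the article does not say how dropouts count. It does not make the figures agree, because inflating for dropout already treats those patients as lost information.

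**The planning rate is conservative.** The section cites placebo rates of 28.7–45.2% and plans on 45%, close to the largest variance in that range for a 10-point difference. With 677 evaluable, the same model gives 79.3% power at a control rate of 40%, 80.0% at 37% and 83.4% at 28.7%. So the slip does not decide whether the trial is adequately sized. The authors' own planning value is 45%, however, and there the shortfall remains.

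**The size may be re-estimated.** The article calls 703 an initial estimate and lets the Data Monitoring Committee revise the size at the interims. That could change the final total but does not correct the starting calculation.

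**Stronger readings.** A reader might infer that the trial is seriously underpowered, or that the late interim counts break type I error control. The documents support neither. The power loss is 1.3 points, and a Lan-DeMets function can spend α at whatever information fraction is actually reached. A reader might also take it as stated that the authors multiplied by 1.2. That is inferred from the numbers, and the finding does not depend on it: however 846 arose, 80% of it is below 703.

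The abstract's total of 864 offers no way out, since 864 × 0.8 = 691. The disagreement between 864 and 846 is a separate point.

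**Conclusion.** The point holds as a minor arithmetic error. The requirement of 703, the 20% dropout and the 846 recruits are inconsistent as written, and nothing elsewhere in the article repairs them. The size is 26 evaluable patients and about 1.3 power points, with no effect on bias, type I error or the analysis.

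The figures rest on 45% against 55%, 2:1 allocation, equally spaced looks, the unpooled variance that reproduces 703, and the condition that all of the 20% contribute no day-90 mRS.

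**What to change.** Keep 846 and correct the sentence in one of two ways: state that it covers about 16.9% dropout with 80% power, or state that a 20% loss of primary-outcome data leaves about 677 evaluable patients and about 78.7% power. Either is wording only and leaves the 564/282 arms unchanged. The cost is a slightly less favorable dropout or power figure. If 20% dropout and 80% power are both to stand, the matching total is 879 (586 + 293), at the cost of 33 more recruits.

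In the same edit, give the interim counts as fractions of the expected evaluable number. Either say that 282 and 564 completers are about 42% and 83% of 677 (or 40% and 80% of 703), or, if thirds are intended, derive the counts from the evaluable number. If the total becomes 879, recompute them from its expected yield of 703.

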### Randomization

All participants will be randomized into the DHI intervention group or placebo control group. The randomization procedure will be performed by the central online randomization system.

### Blinding

All patients, treating physicians and statisticians will be blinded to group assignment until the end of this trial. Considering the different colors of DHI and 0.9 % saline, the dropping bottles will be wrapped in sealed shaded bags (that cannot be unwrapped during infusion; the integrity of these bags will be checked after infusion) and brown infusion devices will be used to conceal the liquid color. Two full-time nurses who cannot contact each other will implement the above procedures independently. One nurse will be responsible for the drug preparation and sealing the dropping bottles with the shaded brown bags in a designated transfusion room; while the other nurse will bring the prepared drugs from the transfusion room to the infusion nurse and supervise the infusion process to ensure the drug allocation is blinded to patients. A confidentiality agreement will be signed by the two full-time nurses before study initiation.

### Interventions

Participants in both intervention and control groups will be provided with standard medical care throughout the trial, which should be in strict accordance with the China Guideline for the Diagnosis and Treatment of Acute Ischemic Stroke (2010) [12], including medical care for vital signs, control of temperature, blood pressure and glucose, improving cerebral blood circulation, antiplatelet treatment and nutritional supportive care. All of these routine treatments will be recorded in patients’ medical records as well as their case report forms (CRFs) in detail. Any concomitant medications that are necessary to manage any serious underlying disease should also be recorded in patients’ medical records and their CRFs. However, any other Chinese herbal medicines or Chinese patent medicines with the similar pharmacological effect of DHI will not be allowed throughout the study period.

#### Intervention group

In addition to standard medical care, participants in the intervention group will be treated with DHI (40 ml, once daily) plus 0.9 % normal saline (250 ml, intravenously, once daily). The infusion rate should be 20–40 drops/min, and the infusion must be completed within 3 hours. DHI cannot be mixed with other liquids to be infused.

#### Control group

In addition to standard medical care, participants in the placebo group will be treated with the DHI placebo (0.9 % normal saline, 40 ml, once daily) plus 0.9 % normal saline (250 ml, intravenously, once daily). The infusion rate should be 20–40 drops/min, and the infusion must be completed within 3 hours. The DHI placebo should be prepared by the full-time nurse.

### Outcome measures

#### Primary outcome

The primary outcome is the proportion of patients with a favorable outcome, defined as a score of 0–1 on the mRS [13] at day 90. The mRS is a commonly used scale for measuring the degree of disability or dependence in the daily activities of people who have suffered a stroke or other causes of neurological disability. The scale runs from 0–6, ranging from perfect health without symptoms to death.

#### Secondary outcomes

The total score of Chinese medicine symptom scales of “*Xueyu Zheng*” (blood stasis syndrome).The proportion of patients with the Barthel Index (BI) score of ≥90. BI uses ten variables to describe the activities of daily living (ADL) and mobility, and a higher number is associated with a better performance of ADL [14].The proportion of patients with an improvement in the NIHSS score of ≥4 or the NIHSS score of 0–1. NIHSS is a tool used to objectively quantify the impairment caused by stroke. A NIHSS score of 0 typically indicates normal function in that specific ability, while a higher score is indicative of some level of impairment [15].The quality of life measured by the EQ-5D scale. The EQ-5D scale has five standard dimensions to measure the generalized health-related quality of life [16].Global disability (mRS ≥3) at day 90.Incidence of new-onset major vascular events within 90 days. Major adverse vascular events include ischemic stroke, hemorrhagic stroke, transient ischemic attack, myocardial infarction and vascular-related death.The safety of DHI is evaluated by the incidences of global disability (mRS ≥3) at day 90, new-onset major vascular events, severe hemorrhages and moderate hemorrhages within 90 days. The definition of “severe hemorrhages” and “moderate hemorrhages” is in accordance with the GUSTO bleeding criteria [17]. Other safety measures include the overall mortality at day 90. All the adverse events (AEs) and serious adverse events (SAEs) within 90 days should be observed and documented. Other outcome measures include the changes in the mRNA and microRNA profiles in 60 patients selected from certain centers. An overview of the measurement data collection schedule is shown in Table 1.

### Interim analysis

As an adaptive trial, two interim analyses will be carried out in a blinded manner after one-third and two-thirds of patients have completed the trial, respectively. Based on the statistical results of the interim analyses, the Data Monitoring Committee (DMC) will decide on the re-estimation of the sample size and subsequent modifications to the trial protocol. As the two interim analyses may lead to an increased possibility of type 1 error, a Lan-DeMets alpha spending function with an O’Brien-Fleming boundary will be used to adjust the results.

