**Methods/Design:**

It is a randomized, multicenter, double-blind, placebo-controlled, adaptive clinical trial. A total of 864 eligible patients will be randomized into either the DHI or placebo group in a 2:1 ratio. All patients will be given the standard medical care as recommended by guidelines. Participants will undergo a 2-week treatment regimen and 76-day follow-up period. The primary outcome is the proportion of patients with a favorable outcome, defined as a score of 0–1 on the modified Rankin scale at day 90. Secondary outcomes include a change in the total score of the Chinese medicine symptom scales of “*Xueyu Zheng*” (blood stasis syndrome), the proportion of patients with a Barthel Index score of ≥90, the proportion of patients with an improvement in NIHSS score of ≥4 or NIHSS score of 0–1, quality of life measured by the EQ-5D scale, etc. Safety outcomes such as global disability (mRS ≥3) at day 90 will also be assessed. The changes in mRNA and microRNA profiles in 96 patients selected from certain centers will also be assessed. As this is an adaptive design, two interim analyses are prospectively planned, which will be carried out after one-third and two-thirds of patients have completed the trial, respectively. Based on the results of the interim analyses, the Data Monitoring Committee (DMC) will decide how to modify the study.

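### Sample size and protocol may be changed on interim results, but the only type I error control named is alpha spending, which does not guarantee the one-sided 5% level if those changes follow the between-arm effect

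*Protocol article*

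**What the plan says.** Three places in the article let interim results reshape the trial.

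- **Abstract, Methods/Design:** "Based on the results of the interim analyses, the Data Monitoring Committee (DMC) will decide how to modify the study".
- **Sample size estimation:** "According to the adaptive design, the sample size may be adjusted after the interim analyses", which fall after one-third and two-thirds of patients have completed.
- **Interim analysis:** on the statistical results of those looks, "the Data Monitoring Committee (DMC) will decide on the re-estimation of the sample size and subsequent modifications to the trial protocol".

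Error control is addressed once, in the Interim analysis section. The sentence begins "As the two interim analyses may lead to an increased possibility of type 1 error, a Lan-DeMets alpha spending function" and goes on to name the O'Brien-Fleming boundary. The reason it gives is the number of looks; adaptation is not mentioned.

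Two further statements bear on the reading. The Interim analysis section says the looks are carried out blinded, and the Blinding section keeps statisticians blinded until the trial ends. The Design section, however, allows early termination if superiority of DHI is seen at an interim analysis.

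**The concern.** A spending function fixes how much error may be used by each information time. It is valid if the information times, including the final one, do not depend on the observed treatment effect. If the final sample size is chosen after seeing that effect, and the ordinary statistic is compared with the same boundary, the chance of a false rejection depends on how the size was chosen. Modifications to the protocol that are left open cannot be covered by any boundary at all.

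At stake is the error rate behind the primary superiority claim on mRS 0–1 at day 90. That claim is already planned at one-sided 5%, so there is little room for further inflation.

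**Working it through.** **Inputs from Sample size estimation.** "the number of subjects was initially estimated to be 703 (one-sided test, α = 0.05, β = 0.2"); "we estimate the proportion is 45 % when placebo coupled with standard medical care are used"; "it is hypothesized that an increase of at least 10 % is of clinical significance for the DHI group", taken as 55% versus 45%; "With a 2:1 randomization ratio, the number of participants in the DHI group is 564 and that in the control group is 282". Looks at information fractions 1/3 and 2/3.

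**Step 1: boundaries.** The O'Brien-Fleming-type spending function is α*(t) = 2[1 − Φ(1.96/√t)] for a one-sided 0.05 total. It spends 0.0007, 0.0164 and 0.0500 by t = 1/3, 2/3 and 1. Solving the three-variate normal gives z boundaries of 3.200, 2.141 and 1.695.

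**Step 2: reproduce 703.**
- Unpooled variance factor at 2:1: 0.55×0.45/(2/3) + 0.45×0.55/(1/3) = 0.37125 + 0.7425 = 1.11375.
- Fixed design: (1.6449 + 0.8416)² × 1.11375 / 0.10² = 688.6.
- Inflation factor for the three looks, 1.0203: 688.6 × 1.0203 = 702.6, which rounds up to 703.

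So 703 is an ordinary three-look group-sequential size, with no allowance for re-estimation.

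**Step 3: why a changed size matters.** Let z₂ be the second-look statistic, B₂ = z₂√(2/3), and T the final size relative to plan. If the final test is the ordinary statistic at 1.695, the conditional rejection probability under the null is Φ[(B₂ − 1.695√T)/√(T − 2/3)].

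| z₂ | T = 1 | T = 2 |
|---|---|---|
| 1.0 (B₂ = 0.816) | Φ(−1.52) = 6.4% | Φ(−1.37) = 8.6% |
| 1.5 (B₂ = 1.225) | Φ(−0.81) = 20.8% | Φ(−1.02) = 15.5% |

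Doubling after a weak trend raises the false-positive chance; doubling after a stronger one lowers it. The net effect therefore depends on the rule.

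**Step 4: overall type I error.** This averages Step 3 over the null distribution of z₂ in the continuation region and adds the probability of an earlier rejection. The article gives no rule, so the following are assumptions: change at the second look only; increases only; cap of 2× the planned size; ordinary final statistic at 1.695. Except in the first and last rows, the size is raised to reach 80% conditional power under the observed trend, or to the cap if that is not reached.

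| Assumed rule | One-sided type I error |
|---|---|
| No change | 5.0% |
| Raise only if conditional power ≥ 30% | 4.8% |
| Raise only if conditional power ≥ 10% | 5.0% |
| Raise on any positive trend | 5.8% |
| Raise whatever the trend | 6.1% |
| Worst increase-only choice | 6.3% |

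With caps of 1.5× and 3×, the positive-trend rule gives 5.6% and 5.9%, and the worst increase-only choice gives 5.9% and 6.8%.

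**Step 5: possible repairs.** Recomputing the final spending boundary for the enlarged size (1.758 at 2×) still leaves 6.0% in the worst increase-only case. A statistic whose stage weights stay at the planned stage sizes, tested at the same boundaries, returns 5.0% for any change of size at the second look.

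**The case against.** The strongest reply has three parts.

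**The article does not define the final statistic.** A reader might infer that an ordinary pooled statistic will be tested against the boundary and that the test is therefore invalid. The article says neither. Lan-DeMets boundaries are compatible with a fixed-weight statistic, and the re-estimation rule, cap and weights may properly stand in the full protocol or analysis plan. This stands: invalidity cannot be claimed, and the absence of those details from an article is not a fault. What remains is that the article does name its control and the reason for it, and that reason covers looks, not an effect-driven size.

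**The looks are said to be blinded.** If re-estimation used only pooled data, spending would be essentially adequate. But stopping for superiority needs a comparison of arms, and the section ties re-estimation to the results of the same interim analyses. A comparative stopping test and an arm-blind re-estimation could coexist, yet nothing in the text says that they do. The wording might mean only that arm labels are masked.

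**Ordinary rules may cause no inflation.** This is right. Declining to enlarge the trial when conditional power is below 10% removes essentially all of it. The article states no such restriction, so this limits the size of the point without removing it.

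**Conclusion.** The point holds as a mismatch between the adaptation described and the error control named. The article allows changes of sample size, and open-ended changes of protocol, on interim results; the spending function it relies on does not guarantee one-sided 5% if those changes follow the between-arm effect.

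The size is conditional. Under the assumptions in Step 4 with a 2× cap, type I error lies between about 4.8% and 6.3%. It should not be read as certain inflation. Nor should figures above 7% be taken as the expected size: a worst case of 7.3% at a 2× cap arises only if the final size may also be cut, here to as little as 0.7 of plan, and is chosen adversarially at each interim value. The documents describe no such rule.

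**What to change.** Choose one of two routes and state it before any comparative interim result is used to change the sample size.

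1. State that re-estimation uses only the pooled, arm-blind mRS 0–1 proportion. The comparative interim test then serves only the stopping boundary.
2. Keep the Lan-DeMets boundaries, but compute the statistic as a fixed-weight inverse-normal (Cui-Hung-Wang) combination of the stages, with weights from the planned stage sizes, together with a pre-set re-estimation rule and cap.

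Under either route, replace the open-ended modification wording with a closed list of what interim efficacy results may trigger: continue, stop on crossing the boundary, or apply the pre-set sample-size rule.

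The cost is mainly wording. Fixed weights lose a little efficiency if the size is raised, and the DMC gives up some discretion.
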